#### 3.4.8. Blood Pressure and Heart Rate

Trained personnel measure blood pressure (BP) and heart rate in the right arm in triplicate with a validated semiautomatic oscillometer (Omron HEM-705CP; Hoofddorp, The Netherlands) (accuracy ± 5 mmHg) while the participant is in a seated position after 5 min of rest. The mean of the three systolic and diastolic BP measurements at 5 min intervals is calculated. BP values of 120/80 mmHg are considered normal references, and the ACC/AHA criteria are used for the diagnosis of arterial hypertension [151].

### 3.5. Blood Parameters

Blood samples are to be collected in the morning (approx. 8:00 am) by trained personnel at the Hospital University La Paz Extraction Unit coinciding with blood tests before chemotherapy to avoid more punctures and hospital visits than necessary. The complete methodology of the blood parameters, specialized biochemical analysis and saliva and stool microbiota are attached as supplementary material (File S3). 

#### 3.5.1. General Biochemical Analysis

General biochemical analysis are carried out in the Biochemistry Laboratory of the Hospital La Paz.

#### 3.5.2. Specialized Biochemical Analysis

Specialized biochemical analyses will be carried out in the Department of Biochemistry and Molecular Biology II University of Granada, Granada, Spain.

##### Plasma and Erythrocyte Collection

Venous blood samples are collected in EDTA-containing tubes and processed within the following 2 h.

##### Urine Collection

A sample of the morning urine is taken using a standardized procedure, aliquoted in 1 mL Eppendorf tubes, and immediately frozen at −80 °C until further analysis.

##### Fatty Acid Profile of Erythrocytes

Erythrocyte lipid extraction. For fatty acid methylation of erythrocytes, the procedure of Lepage & Roy (1988) [152] is followed.

Separation and quantification of fatty acids from erythrocyte lipids. Fatty acid methyl esters are identified and quantified by comparison of retention times with those of previously used authentic standards and confirmation by MS [153].

##### Evaluation of Corporal Oxidative Stress

Determination of 8-iso-PGF2α concentration in urine. The concentration of 8-iso-PGF2α in urine is determined by a highly specific and validated enzyme immunoassay (ELISA) as previously described [154].

Determination of 8-hydroxy-2′-deoxyguanosine concentration in urine. The concentration of 8-OHdG in urine is determined by a competitive enzyme-linked immunosorbent assay as reported elsewhere [154,155].

##### Evaluation of the Antioxidant Defense System

Plasma total antioxidant capacity (TAC). TAC is assessed using a spectrophotometric antioxidant assay kit (709001; Cayman). The ability of the antioxidants in the sample to prevent the oxidation of ABTS^®^ was compared to that of Trolox, a water-soluble tocopherol analog, and quantified as millimolar equivalents of Trolox [156].

Determination of oxidized and reduced glutathione in erythrocytes. A specific kit for the determination of glutathione by colorimetric means is used (Invitrogen, Waltham, MA, USA, catalog number: EIAGSHC (https://www.thermofisher.com/order/catalog/product/EIAGSHC (accessed on 1 October 2023)). 

Erythrocyte antioxidant enzyme activities. The hemoglobin (Hg) concentration in blood samples is determined with a colorimetric cyanmethemoglobin method. The activities of the antioxidant enzymes CAT, GR, GPx, and SOD are assayed by spectrophotometric-specific [157]. 

Determination of plasma antioxidants (retinol, β-carotene, and α-tocopherol). Plasma concentrations of retinol, β-carotene, and α-tocopherol are determined by solvent extraction and ultrahigh-pressure liquid chromatography coupled to mass spectrometry (UHPLC–MS) as reported elsewhere [158,159]. 

##### Plasma Cytokines

Based on previous reports [95,96,97,98], relevant molecules previously described as associated with inflammatory processes and cancer cachexia will be selected for their analysis in plasma. Namely, TNFα, IL-6, IL-1β, IFN-γ, IL-4, IL-10, IL-15, IL-1RA, IL-15, IL-1RA, sIL-6R, sTNFRI, sIL-6R, sTNFRI, sTNFRII, human leukemia inhibitory factor (LIF), human ciliary neurotrophic factor (CNTF) and human proteolysis-inducing factor/dermicidin (PIF/DCD) will be analyzed.

##### Plasma Metabolomics Analysis

A multiplex strategy (GlobalMet from EureCat) will be used for the separation and evaluation of both water-soluble and fat-soluble plasma metabolites (lipidomics) based on semitargeted analysis by GLC–MS (plasma metabolome analysis, nontargeted analysis by UPLC–MS and targeted analysis by UPLC–MS) [160,161,162].

### 3.6. Saliva and Stool Microbiota

#### 3.6.1. Saliva Sampling

The saliva samples obtained during the tests for taste and odor determination are poured into OMNIgene Oral OM-501 (DNA Genotek Inc., Ottawa, ON, Canada) tubes.

#### 3.6.2. Stool Sampling

Samples are collected directly by study participants at home using the OMNIgene Gut OM-200 (DNA Genotek Inc., Ottawa, ON, Canada) and stored immediately at −20 °C.

#### 3.6.3. Flow Cytometry

Microbial loads from saliva and fecal samples will be processed and analyzed by flow cytometry following a standardized procedure [163].

#### 3.6.4. Fecal DNA Amplification and Sequencing

Sequencing of bacterial DNA from both saliva and feces will be performed with a nanopore procedure (MinION™) that enables direct reading of long DNA sequences [164,165].

#### 3.6.5. Saliva and Stool Metagenomics

Potential functional profiles (metagenomic analysis) for the sequenced samples will be predicted using PICRUSt2 [166]. To infer the abundance of each gene family per sample, phylotype abundances will be corrected for their 16S rRNA gene copy number and then multiplied by their functional predictions [167].

## 4. Detailed Procedure

The clinical trial is divided into two phases (Selection and Intervention Phase), which include a selection visit (v0) and five more visits through the study (Figure 1).

### 4.1. Selection Phase

#### Visit 0 (v0, Selection Visit)

After clinical trial approval by the Ethics Committee, patients undergoing neoadjuvant treatment with chemotherapy or chemoradiotherapy for at least three months and malnutrition who were referred to the Clinical Nutrition and Dietetics Unit from the Oncology Service will be invited to participate in the study. If the patient is interested in participating, compliance with the study selection criteria is verified. When all requirements are met, an information-to-read document will be provided. Two researchers are in charge of recruiting patients, explaining the protocol, and providing the informed consent form. Once the patient’s doubts are clarified and if the patient is interested, informed consent will be signed.

During this visit, the following activities are carried out:Nutritional status assessment (GLIM Criteria);Electrogustometry;Taste strips test;Modified Taste and Smell Survey.

The following documentation is given to the patient to complete visit 1 (v1):Daily Food Record (3 days per holiday);Food Frequency Questionnaire;International Physical Activity Questionnaire;Quality of Life Questionnaire.

During this visit, the patient is informed about the next visit date and provided with the following:Blood sample extraction appointment;Stool container for microbiota and metagenome analysis;Urine container for 8-iso-PGF2α determination.

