### 2.1. Participants and Selection Criteria

A total of thirty malnourished cancer patients and taste disorders will be recruited by the Clinical and Dietary Nutrition Unit and Oncology Service of the Hospital University La Paz (HULP), Madrid (Spain).

The inclusion criteria include patients over 18 years of age with cancer and antineoplastic treatment (chemotherapy and any other treatment such as radiotherapy, immunotherapy, etc., for at least three months) who have a weight loss ≥ 5%, malnutrition assessed by the GLIM criteria [23], and taste disturbances measured by electrogustometry. Additionally, these patients must be starting or be in the first three months of antineoplastic treatment, have a life expectancy greater than 3 months, and be capable of oral intake of food and drinks. Patients also must be be at an appropriate cultural level and understand the clinical study, voluntary participation, and sign the informed consent form.

The exclusion criteria include patients participating in another clinical trial, with enteral or parenteral nutrition, poorly controlled diabetes mellitus (HbA1c > 8%), uncontrolled hypertension or hyper/hypothyroidism, severe digestive toxicity due to treatment with chemo-radiotherapy, severe kidney or liver disease (chronic renal failure, nephrotic syndrome, cirrhosis, etc.), severe dementia, brain metastases, eating disorders, a history of severe neurological or psychiatric pathology that may interfere with treatment, alcoholism or substance abuse, severe gastrointestinal diseases, and an unwillingness to consume the miraculin-based food supplement.

The withdrawal criteria include an inability to tolerate the ingestion of the miraculin-based tablets at any dosage or placebo.

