### 2.8. Secondary Outcomes

Clinical trial variables are to be evaluated from the baseline (v0) to the end of the intervention (v5). The mean of the difference between these visits will be compared with those calculated in the other two treatment groups. The evolution of all clinical trial variables will also be evaluated through the different intervention visits where they will be measured (v1, v2, v3, v4, or v5).

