#### 2.8.3. Nutritional Status

Malnutrition is the state resulting from a lack of intake or uptake of nutrition that leads to changes in body composition, reduced fat-free mass and body cell mass, decreased functional capacity, and impaired clinical outcome from disease [40]. This can result from starvation, disease, or aging combined or as separate entities [41]. However, when malnutrition is caused by a concomitant disease, it is referred to as disease-related malnutrition (DRM), where inflammation is usually present [42].

Malnutrition is a condition that is highly prevalent in cancer patients. It is estimated that up to 10–20% of cancer patients die due to malnutrition rather than the tumor [43]. This appears as a consequence of both the tumor and the antineoplastic treatments and negatively affects the quality of life and the effectiveness of treatments. Thus, the assessment of nutritional status in cancer patients is crucial to improve disease prognosis.

Nutritional status is evaluated by the GLIM criteria at the beginning and the end of the intervention (3 months), a period where it is possible to assess the nutritional intervention effect. From the assessment of the nutritional status, a diagnosis of the type of malnutrition presented (moderate or severe) is obtained. Additionally, the nutritional status of the patients will be evaluated at visits 3 and 4 to evaluate the evolution of the patient throughout the clinical trial. For the rest of the variables, the average change occurring from the beginning to the end of the intervention between the different treatments is evaluated.

According to the practical guidelines for clinical nutrition in cancer, nutritional intervention has to lead to increasing oral intake in cancer patients who are malnourished or at risk of malnutrition [43]. In addition to dietary advice, the nutritional intervention is intended to treat symptoms and derangements impairing food intake (e.g., dysgeusia) and offering oral nutritional supplements (ONS) when necessary. In this regard, it is possible that improvement in taste distortions has a positive effect on food intake and, therefore, on the nutritional status of cancer patients.

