BIA performance is to be carried out at scheduled visits v1, v3, v4, and v5. Changes that occurred in BIA parameters month by month were evaluated using the mean of the change and compared between treatments to evaluate the evolution.

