#### 2.8.5. Diet

Inadequate dietary intake is an important factor involved in the weight loss and progressive functional decline associated with advanced cancer [69]. Reduced food intake is a well-established indicator of malnutrition that has strong validity. In this sense, less than or equal to 50% of energy requirements for more than one week, any reduction for more than 2 weeks, or any chronic gastrointestinal condition that adversely impacts food assimilation or absorption is considered reduced food intake or reduced assimilation, an etiologic criterion for malnutrition diagnosis [23].

Diet is collected in the 72 h food daily record at v1, v3, v4 and v5, allowing the transformation of food consumption into energy intake, water, macronutrient intake (proteins, fats (total fat, saturated (SFAs), monounsaturated (MUFAs) and polyunsaturated fatty acids (PUFAs), carbohydrates, fiber, and micronutrient intake (vitamins and minerals)). From this information, it is possible to calculate the caloric and lipid profile as well as the coverage of the recommended intakes of the population. Obtained data are to be evaluated using the European Food Safety Authority dietary reference values [70] and the Nutritional Objectives of the Consensus Document of the Spanish Community Nutrition Society [71]. If food intake does not meet energy requirements, a high-calorie, high-protein oral nutrition supplement with fiber, EPA, DHA, beta-glucans, and enriched in L-leucine (no added sugars) will be prescribed.

Dietary habits, diversity and variety will be measured using a quantitative FFQ. To evaluate the overall dietary habits, the consumption frequency of all food items will be categorized as meeting or not meeting the criteria of the dietary guidelines for the Spanish population [72], the food pyramid for the Spanish population [73], and the nutrition goals for the Spanish population [71].

Malnourished cancer patients with taste distortion and consuming the miraculin-based food supplement are expected to improve their dietary intake from baseline (v0) to the end of the intervention (v5). The mean of the difference between intake and food frequency found between these visits will be statistically compared with those found in the rest of the treatments. The evolution of diet will also be evaluated through the different intervention visits where it will be measured (v1, v3, v4, and v5).

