### 3.2. Malnutrition Criteria

The nutritional diagnosis of malnutrition is established through the GLIM criteria (Global Leadership Initiative in Malnutrition), which classify nutritional status based on phenotypic and etiological criteria [23] (Table 2).

Reduced muscle mass is a phenotypic criterion with strong evidence to support its inclusion in the GLIM consensus criteria. GLIM refers to recommendations from the European Working Group on Sarcopenia in Older People (EWGSOP) [60]. Bioelectrical impedance analysis (BIA) and the body composition method are used to evaluate reduced muscle mass, and hand grip strength functional assessment is considered a supportive measure.

To assess the reduced food assimilation, gastrointestinal symptoms as supportive indicators that can impair food intake or absorption (vomiting, dysphagia, constipation, nausea, diarrhea, or abdominal pain) are considered. They are used as a form of clinical judgment to discern severity based on the degree to which intake or absorption is impaired. Symptom intensity, duration, and frequency are noted.

Inflammation status, major infection, trauma, and acute conditions associated with mild to moderate inflammation are considered. Transient inflammation of a mild degree is not considered a threshold for this etiologic criterion. Chronic disease-related is associated with malignant disease, chronic obstructive pulmonary disease, congestive heart failure, chronic renal disease, or any disease with chronic or recurrent inflammation. Indeed, C-reactive protein (CRP) is used as a supportive laboratory measure of inflammation.

The GLIM criteria require at least one phenotypic criterion and one etiologic criterion to diagnose malnutrition. Malnutrition seriousness is determined based on the phenotypic criteria classifying it as moderate or severe malnutrition [23] (Table 2).

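### The baseline GLIM grade is tied to v0, before the bioimpedance muscle-mass measurement exists, so a v0-to-v5 contrast can turn an unchanged moderate patient into a severe one

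*Protocol article*

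**What the plan says.** All references are to the protocol article.

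- **Grading at v0.** Section 4.1 puts "Nutritional status assessment (GLIM Criteria" first among the v0 activities, which it gives as "Nutritional status assessment (GLIM Criteria);Electrogustometry;Taste strips test;Modified Taste and Smell Survey". No bioimpedance is listed there. The v1 list in Section 4.2.1 includes bioimpedance and does not repeat the GLIM assessment.
- **Contrast.** Section 2.8 states: "Clinical trial variables are to be evaluated from the baseline (v0) to the end of the intervention (v5".
- **This outcome.** Section 2.8.3 states: "Nutritional status is evaluated by the GLIM criteria at the beginning and the end of the intervention (3 months". It adds v3 and v4 but gives no visit number for the beginning.
- **Muscle mass.** Section 3.2 states: "Bioelectrical impedance analysis (BIA) and the body composition method are used to evaluate reduced muscle mass". The Electrical Bioimpedance part of Section 2.8.4 states: "BIA performance is to be carried out at scheduled visits v1, v3, v4, and v5".
- **Severity.** Section 3.2 and Table 2 set moderate or severe from the phenotypic criteria: weight loss, BMI and muscle mass.
- **Entry.** Section 2.1 admits patients "who have a weight loss ≥ 5%, malnutrition assessed by the GLIM criteria [23], and taste disturbances measured by electrogustometry".

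**The concern.** Nutritional status by GLIM is in the title and the abstract, so readers will look at this outcome closely even though it is secondary. A change in grade is interpretable only if both grades use the same inputs. Read as written, the only GLIM assessment listed before the first tablet is the one at v0, when one of the three severity-setting criteria has no scheduled measurement. By v5 that measurement exists. A patient can then cross from moderate to severe because the information changed, not because the patient did. In a pilot with very small arms, a few such shifts could hide a real improvement in the grade.

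**Working it through.** The article states no numerical figure for this point, so there is none to reproduce. The check has three steps.

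**1. Schedule, side by side**

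| Item | First listed | Where |
|---|---|---|
| GLIM assessment | v0 | Section 4.1 |
| Bioimpedance (muscle mass) | v1 | Sections 2.8.4 and 4.2.1 |
| 72 h food record, collected | v1 (handed out at v0) | Sections 2.8.5, 4.1 and 4.2.1 |
| Blood sample (CRP) | v1 (appointment given at v0) | Sections 4.1 and 4.2.1 |
| First tablets | v1 | Section 4.2.1 |

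The article is not consistent about the beginning. Section 2.8.6 equates it with v0, while Sections 2.8.7, 2.8.8 and 2.8.9 equate it with v1.

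**2. What the missing input can do to the grade**

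Rule from Section 3.2 and Table 2: a diagnosis needs at least one phenotypic and one etiologic criterion, and severity comes from the phenotypic criteria. I read this as severity = the worst phenotypic level. Malignant disease counts under the inflammation criterion, so every participant already has an etiologic criterion.

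Take a patient who does not change and who has at least moderate weight loss, as entry implies. Score each phenotypic criterion 0 (absent), 1 (moderate) or 2 (severe).

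- Patterns: weight loss (1, 2) × BMI (0, 1, 2) × muscle mass (0, 1, 2) = 2 × 3 × 3 = 18.
- Grade without muscle mass = max(weight loss, BMI). Grade with it = max(weight loss, BMI, muscle mass).
- The two differ in 2 of 18 patterns: (1, 0, 2) and (1, 1, 2). These are moderate weight loss, BMI normal or moderate, and a severe muscle deficit. Both go from moderate to severe. None goes the other way.
- Adding food intake (no/yes) and CRP (no/yes) gives 18 × 2 × 2 = 72 combinations. Those two inputs change the diagnosis or severity in 0 of 72. Muscle mass raises the grade in 2 × 2 × 2 = 8 of 72.

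These are counts of logical patterns, not patient frequencies. The article reports no distribution of muscle mass.

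**3. Weight of one patient**

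Section 5 reports 21 completers. The percentages of women in Table 3 fit 5/8, 2/6 and 6/7, which gives arms of 8, 6 and 7. As a check, 5 + 2 + 6 = 13 and 13/21 = 61.9%, as reported. One shifted patient moves an arm's proportion severe by 1/8 = 12.5, 1/6 = 16.7 or 1/7 = 14.3 percentage points.

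The average completer had lost 7.60% of body weight and had a BMI of 22.37 kg/m² at a mean age of 59.8 years. By Table 2 those means correspond to moderate weight loss and no low-BMI criterion, which is one of the two backgrounds where muscle mass decides the grade. Means do not say how many individuals fit that description.

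**The case against.** The strongest reply is that the outcome contrast may never use the v0 grade. Section 2.8.3 does not name v0, tablets start at v1, and three sections call v1 the beginning. The wording in Section 2.8 cannot be fully literal, because the functional test and diet are also given a v0 baseline while being measured first at v1 (for diet: "Diet is collected in the 72 h food daily record at v1, v3, v4 and v5"). The v0 list is also not exhaustive: study weight and BMI are listed from v1 too, yet some such data must be at hand to apply GLIM at all. The schedule figure and the supplementary visit details are not shown. A baseline completed with v1 data is therefore a plausible intention. That stands as a limit on certainty, but no text says the grade is completed at v1, and Sections 2.8, 2.8.3 and 4.1 would still need to be reconciled.

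A reader might also infer more than the article supports:

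- *That missing food intake and CRP distort the grade.* They do not. Severity is phenotypic only, CRP is only supportive, and malignancy already supplies the etiologic criterion.
- *That entry is unsound because muscle mass is unknown at v0.* It is not. Weight loss of at least 5% is required separately and, with cancer, suffices for a GLIM diagnosis. The one exception is a loss of exactly 5%, which Section 2.1 admits and Table 2 (more than 5%) does not count.
- *That the treatment comparison is biased.* The same rule applies in all arms, so the shift does not by itself favour one.

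**Conclusion.** The point holds in a narrow form. The text ties the baseline GLIM grade to a visit without the muscle-mass measurement, and it does not say clearly which visit supplies the baseline. If v0 is the comparator, an unchanged patient with a severe muscle deficit and no other severe criterion appears to worsen. The error runs one way and affects 2 of 18 phenotypic patterns. It adds misclassification and can mask improvement.

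This rests on three assumptions: that the v0 grade is made without bioimpedance, that any single severe phenotypic criterion makes the grade severe, and that a severe deficit is actually graded from bioimpedance at later visits. On the last, Table 2 says only that the deficit is severe, and Section 2.8.4 gives one cut-off for low muscle mass. Merely reduced muscle mass would not change the grade of a patient who already has moderate weight loss. The number of patients affected cannot be estimated from the article, and any prevalence put on it would be a guess.

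**What to change.** - Keep the v0 GLIM assessment as the screening assessment. Eligibility does not need to be reconfirmed at v1, because adding muscle mass cannot make a GLIM-positive patient negative.
- Define the baseline GLIM grade from the v1 weight, BMI and bioimpedance data, taken before the first tablet.
- Use the same phenotypic inputs, graded the same way, at v3, v4 and v5, and define the GLIM contrast as v1 to v5.
- Reconcile Sections 2.8, 2.8.3 and 4.1 accordingly.
- Regrade the baseline of patients already enrolled from their stored v1 data.

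With identical inputs at both ends, the artificial shift for an unchanged patient is zero by construction. The cost is a few amended sentences and a regrade of up to 31 baseline records, the number randomized according to Section 5. No additional measurement is required.
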